### **Secondary objectives/outcomes:**

A two-sided generalized Wilcoxon test will also be used to compare times to critical actions, excluding the primary outcome. The number of participants who did not recognize and treat the underlying condition of the TCA, and the number of participants declaring the patient dead prematurely, will be compared between groups calculating the chi-square test. Protocol deviations will be analyzed separately for each protocol deviation listed in Table 2. The respective frequencies of each protocol deviation will also be compared between groups calculating the chi-square test. Fisher's exact test will be used if one or more expected cell frequencies are less than 5.

In addition, the Wilcoxon rank sum test will also be used to compare the gaze behavior (dwell-time in AOIs, fixation count and average fixation duration, and relative time when no AOI is illustrated) and the NASA-TLX scores (global and per objective) between randomized groups.

Furthermore, a multivariable Cox regression model (including an interaction term) will be used to determine the influence of gender on the primary outcome, and the potential modifying effect of gender on the training effect (= group effect). The HEXACO subscale and the Technology Readiness Score will also be included in the multivariable model to adjust for potential imbalances between the randomized groups.

The following Spearman correlation coefficients will be calculated corresponding to the remaining secondary objectives:

- Correlation of 5-point Likert scales between the frequency of playing classic video games and the primary outcome

5-point Likert scales, the incidence rate of VR-related AEs, and the SUS scores will be reported using descriptive statistics only.

Observations with missing data in the primary outcome measure will be excluded from statistical analyses. Boxplots will be used to illustrate calculations. A two-sided p-value of  $< 0,05$  will be considered statistically significant.

Due to the singular primary objective, no correction for multiple testing will be made. All secondary objectives are exploratory in nature and will be used to generate further hypotheses.

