### 3.2.1 Randomization

Recruited participants will be randomly assigned to the control or intervention group on an equal basis by gender. Participants will not know their allocation to either group until they have watched the entire introductory video and completed Questionnaire 1. Randomization will be performed using the web-based randomization software Randomizer from MedUni Vienna (38).

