#### 3.4.1 Variables

**Table 3.** Variables to be collected in this study

| Variable                                  | Data source     | Notes                                                                                                                |
|-------------------------------------------|-----------------|----------------------------------------------------------------------------------------------------------------------|
| Baseline characteristics           |                 |                                                                                                                      |
| Age                                       | Questionnaire 1 | <24; 24 – 27; 28 – 29; 30 – 32; >32 (in years)                                                                       |
| Gender                                    | Questionnaire 1 | Male/female/divers/inter/open/none                                                                                   |
| Knowledge of German                       | Questionnaire 1 | First language/fluent/basic                                                                                          |
| Experience                                | Questionnaire 1 | Junior physician (common-trunk) or first-year resident (anesthesia/intensive care; emergency medicine; traumatology) |
| Previous participation in ERC ALS courses | Questionnaire 1 | Yes/no                                                                                                               |

|                                                                                |                 |                      |
|--------------------------------------------------------------------------------|-----------------|----------------------|
| Previous participation in certified advanced trauma courses (PHTLS, ETC, ATLS) | Questionnaire 1 | Yes/no               |
| Real Life in-hospital CPR experience                                           | Questionnaire 1 | 5-point Likert scale |
| Real life out-of-hospital CPR experience                                       | Questionnaire 1 | 5-point Likert scale |
| Real life in-hospital trauma management experience                             | Questionnaire 1 | 5-point Likert scale |
| Real life out-of-hospital trauma management experience                         | Questionnaire 1 | 5-point Likert scale |

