### **Primary objective/outcome:**

A two-sided generalized Wilcoxon test with a 5% significance level will be used to compare the primary outcome between the randomized groups. Participants who do not identify and treat the underlying condition of TCA will be censored at 15 minutes. Furthermore, if patients are declared dead prematurely, the observation will also be censored at 15 minutes.

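### The covariates named to adjust for imbalance are two attitude scores; prior courses, experience and training level, all recorded before randomisation, enter no model

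*Protocol*

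**What the plan says.** - **Primary analysis** (Protocol 3.5, Primary objective/outcome): "A two-sided generalized Wilcoxon test with a 5% significance level will be used to compare the primary outcome between the randomized groups". No covariate enters this test.
- **The only multivariable model** (3.5, Secondary objectives/outcomes): "a multivariable Cox regression model (including an interaction term) will be used to determine the influence of gender on the primary outcome", and to examine whether gender modifies the training effect. The model therefore holds group, gender and their interaction.
- **Covariates for imbalance** (same section): "The HEXACO subscale and the Technology Readiness Score will also be included in the multivariable model to adjust for potential imbalances". The same section calls all secondary objectives exploratory.
- **Randomisation** (3.2.1): participants are "randomly assigned to the control or intervention group on an equal basis by gender". No other balancing factor is named.
- **Baseline items** (3.4.1, Table 3): these include "Previous participation in ERC ALS courses" and "Previous participation in certified advanced trauma courses (PHTLS, ETC, ATLS" (each yes/no), and "Real life in-hospital trauma management experience" with its out-of-hospital and CPR counterparts (5-point scales). Training level, common trunk or first-year resident, is also recorded. All come from Questionnaire 1, which section 3.2 places before randomisation.
- **Drop-out criteria** (3.1.3): using other trauma or CPR training during the study leads to withdrawal.

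**The concern.** The primary outcome is the time a team leader takes, after CPR starts, to reach mini-thoracotomy in a traumatic arrest. Earlier ALS or trauma courses, real trauma and CPR experience, and stage of training are the baseline items with the most direct claim to predict that time. The scenario is modelled on the ERC course assessment format (3.2.3). Eligibility (3.1.1) mixes common-trunk physicians with first-year residents and does not exclude people who have taken courses.

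The protocol states an aim, adjustment for imbalance, and fixes a covariate set for it that contains none of these items. This is a stated choice that serves its own aim poorly, not a detail left open. If one arm happens to hold more course-trained doctors, no planned estimate would take that into account, and covariates picked after the data are seen would look data-driven.

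**Working it through.** **1. The plan's own sample size.** The Noether formula with P = 0.71, two-sided 5% and 80% power gives N = (1.960 + 0.842)² / (12 × 0.25 × 0.21²) = 7.85 / 0.1323 = 59.3, so 30 per group. With 10% drop-out, 60 / 0.90 = 66.7, so 67. Both match section 3.3, and nothing here disputes them.

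**2. How often chance imbalance arises.** The documents give no prevalence of prior courses, so 20%, 30% and 50% are assumed. With 60 participants split 30:30, the number of course-trained people in one arm is hypergeometric. At 30% there are 18 in all. A 9:9 split has probability C(18,9)·C(42,21)/C(60,30) = 0.221, and 8:10 or 10:8 together have 0.380. Every other split gives a gap of at least 4/30 = 13.3 points, with probability 1 − 0.221 − 0.380 = 0.399.

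| Course-trained (assumed) | Gap ≥ 13 points | Gap ≥ 20 points |
|---|---|---|
| 20% | 33% | 10% |
| 30% | 40% | 16% |
| 50% | 44% | 20% |

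**3. What such a gap does to the estimate.** Under proportional hazards, P = 0.71 corresponds to a group hazard ratio of 0.71/0.29 = 2.45, log 0.90. As an approximation, a gap d in a covariate with hazard ratio h shifts the log hazard ratio by d × ln h. With d = 0.133:

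- h = 1.5: 0.133 × 0.405 = 0.054, about 6% of the planned effect
- h = 2: 0.133 × 0.693 = 0.092, about 10%
- h = 3: 0.133 × 1.099 = 0.146, about 16%

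**4. What adjustment buys in a Cox model.** This is an illustrative simulation: 1,000 trials per cell, 30 per arm, group hazard ratio 2.45, exponential times with control hazard 0.12 per minute, censoring 13 minutes after CPR start, and 30% course-trained. All values other than the arm size and P = 0.71 are assumptions. Gender and the interaction were left out. One model carried two scores unrelated to outcome; the other carried prior training.

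| Hazard ratio for prior training (assumed) | Power, two scores | Power, prior training | Gain (points) | Median group HR, two scores | Median group HR, prior training |
|---|---|---|---|---|---|
| 1.5 | 87.4% | 90.0% | 2.6 | 2.50 | 2.48 |
| 2 | 86.5% | 90.6% | 4.1 | 2.42 | 2.54 |
| 3 | 82.5% | 89.0% | 6.5 | 2.24 | 2.48 |

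Each power has a simulation standard error of about √(0.87 × 0.13/1000) = 1.1 points, and a difference between two has about 1.1 × √2 = 1.5. The smallest gain is therefore barely distinguishable from noise. The low 2.24 in the last row arises because leaving out a strong predictor pulls a hazard ratio towards 1 even in balanced arms. It is not confounding.

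**5. Parameters.** With gender as two categories, the gender model has 5 terms: group, gender, interaction and two scores. Replacing the scores with two yes/no training covariates keeps it at 5. A main-effects model with group, gender, prior course and training level has 4. At most 60 events gives 60/5 = 12 or 60/4 = 15 per term. If 45 to 55 participants reach the event (assumed), that falls to 9–11 or about 11–14.

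**The case against.** The strongest reply is that the Cox model exists to study gender, not to estimate the training effect, and is labelled exploratory. The unadjusted primary test is made valid by randomisation, and chance imbalance is already covered by its 5% error rate. That stands. A reader might infer that the primary result is biased, or that its error rate is inflated; the documents support neither. Nor would the change recover power in the primary test, which stays unadjusted.

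It can also be said that a supportive analysis may be added in the statistical analysis plan, which is not shown. This is true of the extra model. It does not answer the covariate choice, which the protocol itself fixes together with its purpose.

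Third, no passage shows that prior courses predict time to mini-thoracotomy better than openness or technology readiness. The population is narrow, everyone sees the same introductory video, and the two scores may bear on response to VR. This stands as a limit: prognostic strength is a reasoned assumption. It is not arbitrary, since the protocol withdraws participants for the same kind of training taken during the study. Nor do the documents show that the two scores are worthless, so they should be kept, in a separate model.

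**Conclusion.** The concern holds in a limited form. The covariates chosen for imbalance adjustment leave out every recorded measure of prior training and experience, and nothing in the design balances those measures. The cost is a weak check against chance imbalance and some precision in the Cox estimate. Moderate imbalance is common at this size: a gap of 13 points or more in 33% to 44% of randomisations for assumed prevalences of 20% to 50%. Its effect on the log hazard ratio is modest, about 6% to 16% of the planned effect, and the gain in Cox power is about 3 to 6 points, for assumed hazard ratios of 1.5 to 3. Prevalence, prognostic strength and event count are all assumed. The point merits a wording change because the data will be collected anyway.

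**What to change.** In section 3.5:

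1. Pre-specify one supportive main-effects Cox model for the primary outcome with group, gender, any prior ALS or certified trauma course (yes/no) and training level (common trunk versus first-year resident). Report the adjusted group hazard ratio with its 95% CI. A main-effects model is needed because, with the interaction present, the group coefficient refers to one gender only.
2. Use the same one or two training covariates for imbalance adjustment in the gender-by-group model.
3. Keep the HEXACO subscale and the Technology Readiness Score in a separate exploratory model.

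The primary test and the sample size do not change, and no new data are needed. The downside is limited events per parameter with about 60 participants. Covariates must stay few, which is why the two course items are merged and the four experience scales are left out of the model.

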To address this issue, innovative, less expensive, and more accessible training methods need to be developed. Virtual reality (VR) simulation is an emerging approach that enables realistic and immersive training scenarios without the need for expensive equipment or physical space (11,16–18). In-situ simulation, on the other hand, allows for training in the actual clinical environment, allowing for the assessment of team dynamics and human factors that may affect resuscitation outcomes. The combination of pre-course VR preparation (15,19) and in-situ simulation approaches (15,19–21) could ultimately improve the TCA management skills of HCPs and also have a positive impact on the outcomes of critically injured patients. Blended learning approaches appear to provide the best educational value for CPR training (15,20,22–24).

Therefore, the primary aim of this study is to evaluate the effectiveness of using VR technology, as opposed to e-learning (19,25–27) preparation, to equip learners with the skills and knowledge necessary for in-person simulation training and to improve their performance in TCA management skills. The secondary aims are to assess gender differences in performance (28,29), the frequency of protocol deviations, the cognitive load, and the gaze behavior between groups as well as participants' acceptance and impressions of VR in medical education.

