### 2.3 Secondary Objectives

- 1) Comparing the number of participants who did not recognize and treat the underlying condition (one or more missed critical actions) of the TCA between randomized groups.
- 2) Comparing the number of participants who prematurely declared a patient dead (before the 15-minute time limit of the scenario).
- 3) Comparing the time to critical actions, excluding the primary outcome measure, between randomized groups.
- 4) Comparing the proportions of the respective protocol deviations between randomized groups.
- 5) Evaluate gender differences in the primary outcome.
- 6) Comparison of cognitive load between the randomized groups while performing the simulated assessment scenarios as measured by the National Aeronautics and Space Administration Task Load Index (NASA TLX).
- 7) Eye-tracking
  - a) Comparing the gaze behavior (dwell-time in AOIs, fixation count, and average fixation duration) between randomized groups.
  - b) Comparing the relative time when no AOI is illustrated between randomized groups.
- 8) Using a 5-point Likert scale:
  - a) Participants' subjective impressions of their learning progress when using VR/e-learning.

- b) Participants' subjective impressions of their level of frustration when using VR/e-learning.
  - c) Participants' subjective impression of their level of enjoyment when using VR/e-learning.
  - d) Participants' subjective confidence in recognizing and providing initial care to polytraumatized patients in cardiac arrest in the simulation sessions.
  - e) Participants' subjective overall performance in the simulation sessions.
  - f) Participants' overall performance in the simulation sessions from the expert's point of view.
- 9) To assess the correlation between how often participants have played VR and non-VR video games in the past 12 months and between the ages of 6 and 18 and the primary outcome?
- 10) The incidence rate of VR-related adverse events (AEs).
- 11) System usability scale (SUS) for the use of the VR simulations.

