## 3.2 Study design

This study is a single-center, prospective, single-blind, randomized, controlled trial. It aims to assess the efficacy of VR as a more effective preparation method for in-person simulation trainings, compared to e-learning. The focus is on improving physicians' trauma CPR management skills.

All recruited participants will watch a 60-minute video to learn about the requirements, steps, and other important information about this study. Furthermore, this introductory video will give an overview of management strategies for trauma patients going into cardiac arrest in an in-hospital setting and provides links to the guidelines (30–32) on which this study is based. It also indicates that knowledge of the content of the guidelines is a prerequisite for Phases 2 through 3. This video can be viewed as often as desired throughout the study. Participants will also be required to complete the electronic Questionnaire 1 (Additional file #2) prior to randomization, which assesses participants' baseline characteristics (including the German versions of the "Openness to Experience" subscale of the 100-item HEXACO-PI-R test (33,34) and the Technology Readiness Scale (35)).

Each participant will then complete either the e-learning course (control group) or the VR training simulations (intervention group) over a two-week period, both focusing on the same content. Both groups will spend approximately the same amount of time learning the same content, which will prepare the participants for the assessment in the simulation session. If participants do not complete the entire e-learning course or all four VR simulations, they will be dropped from the study.

After Phase 2, all participants will attend the simulation session and will be evaluated in the role of medical team leader of a standardized TCA scenario (Phase 3).

In addition, each participant will be required to complete Questionnaire 2 (Additional file #3) immediately following the simulation session in Phase 3. Only the intervention group will be required to complete the VR system usability portion of this questionnaire. The system usability scale (SUS) (36,37) will be translated and used in German.

[figure not shown]

**Figure 1.** The course of events during the study.

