| Openness to Experience Score (HEXACO subscale)                                 | Questionnaire 1 | 1 to 5               |
| Technology Readiness Score                                                     | Questionnaire 1 | 12 to 60             |
| Experience with non-VR video games within the last 12 months                   | Questionnaire 1 | 5-point Likert scale |
| Experience with VR video games within the last 12 months                       | Questionnaire 1 | 5-point Likert scale |
| Experience with non-VR video games at the age of 6 to 18 years                 | Questionnaire 1 | 5-point Likert scale |
| Experience with VR video games at the age of 6 to 18 years                     | Questionnaire 1 | 5-point Likert scale |
| Desire for more digital tools in medical education                             | Questionnaire 1 | 5-point Likert scale |
| Primary outcome                                                         |                 |                      |
| Time to critical action #3                                                     | Scoring sheet   | Minutes : seconds    |
| Secondary outcomes                                                      |                 |                      |
| Recognition and treatment of the underlying condition                          | Scoring sheet   | Yes/no               |
| Patient declared dead prematurely                                              | Scoring sheet   | Yes/no               |
| Times to critical actions #1 and #2                                            | Scoring sheet   | Minutes : seconds    |
| Protocol deviations                                                            | Scoring sheet   | Yes/no               |
| NASA-TLX (global and per objective)                                            | Questionnaire 2 | 0 to 100 points      |
| Eye-Tracking                                                                   | Scoring sheet   |                      |
| - Dwell time in AOs                                                            |                 | Minutes : seconds    |
| - Fixation count                                                               |                 | Count                |
| - Average fixation duration                                                    |                 | Minutes : seconds    |
| - Relative time without AOI                                                    |                 | Minutes : seconds    |

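### Objective 5 asks for the gender difference in the primary outcome, but the only model named gives the difference at equal Openness and Technology Readiness

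*Protocol*

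**What the plan says.** Protocol section 2.3, objective 5, reads "Evaluate gender differences in the primary outcome". The Background puts the aim in the same unconditional way: "The secondary aims are to assess gender differences in performance".

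Section 3.5, under the secondary objectives, names one analysis for this, a multivariable Cox regression with an interaction term, which "will be used to determine the influence of gender on the primary outcome" and also serves to examine whether gender modifies the training effect. It continues: "The HEXACO subscale and the Technology Readiness Score will also be included in the multivariable model", with the purpose "to adjust for potential imbalances between the randomized groups". Table 3 in section 3.4.1 identifies the HEXACO subscale as Openness to Experience. No gender comparison without the two scores is described.

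Both scores come from the baseline questionnaire; under section 3.2 participants must "complete the electronic Questionnaire 1 (Additional file #2) prior to randomization". Section 3.2.1 has allocation done "on an equal basis by gender", so gender is balanced across the groups but is not itself randomised. Section 3.5 calls all secondary objectives exploratory.

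**The concern.** One model is asked to do two jobs. For the training effect, adjusting for two scores measured before randomisation is sound. For gender, the stated reason does not carry over, because balance between randomised groups says nothing about how the genders compare. Openness and technology readiness are self-rated traits that may differ by gender and may affect performance. Holding them fixed removes any part of the gender difference that runs through them.

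The reported gender hazard ratio then answers a narrower question than objective 5 asks, and nothing in the protocol tells the reader so. The result is meant to generate hypotheses, and a difference at equal traits suggests other hypotheses than an overall difference does. This is separate from the coding of the interaction term and remains if that term is dropped.

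**Working it through.** **The plan's own figure.** The protocol gives no figure for objective 5. The sample size in section 3.3 reproduces and is not in dispute. Noether's formula gives N = (1.960 + 0.842)² / (12 × 0.25 × (0.71 − 0.50)²) = 7.85 / 0.1323 = 59.3, so 30 per group. Allowing for 10% drop-out, 60 / 0.9 = 66.7, so 67. The analysed sample is taken as 60 below.

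**What the coefficient means.** Let a be the gender difference in a trait, in SD, and b the log hazard ratio per SD of that trait. To a good approximation,

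overall gender log HR = log HR at equal traits + a × b.

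The planned model reports the first term on the right. Objective 5, as worded, asks for the left side. The two agree only if a or b is near zero. With a and b of either sign, the shift can go in either direction.

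**Inputs.** The documents give neither a nor b. Assumed ranges are a = 0.3 to 0.7 SD and b = 0.2 to 0.4 log hazard per SD.

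| a | b | a × b | HR factor, exp(a × b) | a × b ÷ 0.31 |
|---|---|---|---|---|
| 0.3 | 0.2 | 0.06 | 1.06 | 0.19 |
| 0.5 | 0.3 | 0.15 | 1.16 | 0.48 |
| 0.7 | 0.4 | 0.28 | 1.32 | 0.90 |

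The 0.31 is the SD of the gender log HR in simulated Cox fits with n = 60 and an assumed 15% censored. The shift stays below one standard error throughout.

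**Simulation with no direct gender effect, n = 60 (400 fits each).** For a = 0.5 and b = 0.3, the gender HR was 1.18 without the trait and 1.02 with it, a ratio of 1.16. For a = 0.7 and b = 0.4, it was 1.27 and 0.99, a ratio of 1.28. The product rule slightly overstates the second.

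**Larger samples (8,000 simulated participants, training HR assumed to be 2).** The trait gap is now set in the other direction, so the HRs fall below 1. Gaps of 0.3, 0.5 and 0.8 SD with log HR 0.3, 0.4 and 0.5 per SD gave overall HRs of 0.90, 0.84 and 0.69, against 0.98, 1.01 and 1.01 with the traits included. With no gender gap in the trait the two nearly agreed (0.96 and 0.97, true value 1.0), which also shows the simulation error.

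**Does this change a significance result?** With standard error 0.31, ln(1.18) / 0.31 = 0.53 and ln(1.27) / 0.31 = 0.77. Two-sided 5% power is Φ(0.53 − 1.96) + Φ(−0.53 − 1.96) = 8%, and by the same formula 12% for the second. Even the model without the scores would therefore rarely declare differences of this size significant.

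**The case against.** **A covariate-adjusted gender association is a legitimate exploratory target.** Objective 5 does not expressly promise an unconditional difference. This stands in part: the sponsor may want the conditional quantity. But the protocol does not say so, and its only reason for the scores concerns the randomised groups.

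**The mechanism is assumed.** This stands. No section says that either trait differs by gender or affects the time to mini-thoracotomy. Without a gender gap in the traits, the two estimates nearly coincide.

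**The model without the scores has faults of its own.** This also stands. Section 3.1 recruits volunteers by notice board, e-mail and social media. If technology-minded people of one gender volunteer more readily, the unadjusted contrast reflects recruitment: with that selection, log HR 0.4 per trait SD and no true gender effect, a simulation gave 1.25 unadjusted and 1.01 adjusted. Leaving out a prognostic covariate also pulls a Cox HR towards 1: with no gender gap and a true HR of 1.67, the simulated values were 1.60 without the trait and 1.68 with it. The documents cannot decide between the two models, which is why both should be reported.

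**A stronger reading is tempting:** that a real gender difference will be reported as absent. With an assumed direct gender HR of 0.6 pointing the same way as the trait effect, simulated power at n = 60 falls from about 64% to 40% (gap 0.5 SD, log HR 0.4 per SD), or from 80% to 43% (0.8 SD, 0.5). The documents support none of those inputs. Under the smaller assumptions above, neither model has useful power.

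**A supplementary model could be left to the SAP.** True in general, but here the protocol itself fixes the model and its covariates, and the point concerns what it fixes.

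**Conclusion.** As written, the plan yields only a conditional gender estimate for an objective worded without conditions, for a reason that does not apply to gender. This follows from the text alone. The size does not: the factor of about 1.06 to 1.32 rests on assumed trait gaps and trait effects and is less than one standard error at n = 60. The consequence is a gender hazard ratio open to misreading. The documents do not establish that a true difference would be hidden, nor that the adjusted model is wrong in itself. Severity is minor: objective 5 is exploratory, and the primary test and sample size are untouched.

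**What to change.** In section 3.5, add for objective 5 a Cox model with group and gender only. Report its gender hazard ratio with 95% CI as the overall gender difference, and report the trait-adjusted estimate beside it, labelled 'at equal traits'. Keep both scores in the model for the group effect and its modification by gender. If the conditional question is the one intended, objective 5 should say so.

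The cost is one sentence and one further model fit from data already collected; the group comparison does not change. The downsides are one more exploratory estimate, and that the estimate without the scores may be slightly attenuated and can reflect who volunteered. A short note to that effect beside the result is enough.

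### The Spearman coefficients planned for objective 9 carry no arm or gender term, so they are slightly diluted, would average any arm-specific gaming effect and may pick up gender

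*Protocol*

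**What the plan says.** Objective 9 in section 2.3 reads "To assess the correlation between how often participants have played VR and non-VR video games in the past 12 months", and goes on to cover gaming between the ages of 6 and 18. The other side of the correlation is the primary outcome, the time from the start of chest compressions to the mini-thoracotomy. Table 3 (section 3.4.1) collects four 5-point gaming items before randomization: VR and non-VR games, each for the two periods. One of them is "Experience with non-VR video games at the age of 6 to 18 years".

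Section 3.5 gives the method: "The following Spearman correlation coefficients will be calculated corresponding to the remaining secondary objectives". A single item follows: "Correlation of 5-point Likert scales between the frequency of playing classic video games and the primary outcome". It mentions no stratification by arm, no partial coefficient and no gender term.

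Elsewhere the protocol takes both factors into account. Allocation is balanced on gender: "Recruited participants will be randomly assigned to the control or intervention group on an equal basis by gender". For objective 5, "a multivariable Cox regression model (including an interaction term) will be used to determine the influence of gender on the primary outcome", and that model also covers the training effect and its modification by gender. Gaming is not named in it. The section adds: "All secondary objectives are exploratory in nature and will be used to generate further hypotheses".

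**The concern.** The protocol has chosen a method for objective 9, and read naturally it is a raw coefficient over all participants. Three things can blur it.

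- **Dilution.** The trial is sized on a sizeable training effect on this same outcome. In a pooled correlation the spread between arms acts as noise.
- **Averaging.** Gaming may help someone learning with a headset and controllers more than someone taking an e-learning course. Section 3.2.2 gives the VR arm alone an orientation module of about 20 minutes so that the technology does not distract from the content. Technical familiarity is therefore a factor the protocol itself recognises. A pooled coefficient cannot show an effect confined to one arm.
- **Gender.** The protocol investigates gender as a determinant of the outcome. If gaming frequency also differs by gender, a raw coefficient cannot separate the two.

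What is at stake is how useful the result is for generating hypotheses. The primary analysis is not touched.

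**Working it through.** **Inputs from the protocol.** Section 3.3: 30 per group, 80% power, a probability of 0.71 that an observation in one group is smaller than one in the other, two-sided 5%, 10% drop-out, 67 recruited. The protocol gives no figure for objective 9, nor for how gender relates to gaming or to time. Those values are assumed below. Correlations are given as absolute sizes unless marked.

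**The plan's own figure.** Noether's formula gives N = (1.960 + 0.842)² / (12 × 0.25 × (0.71 − 0.5)²) = 59.3, so 60 in total. Then 60 / 0.9 = 66.7, so 67. Both stated sizes are reproduced, and 0.71 can be used as the planning effect.

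**1. Dilution.** On a scale where the outcome is normal, 0.71 is a shift of d = √2 × z(0.71) = 0.783 SD. Pooling two equal arms adds d²/4 to the within-arm variance, so a within-arm correlation is multiplied by 1/√(1 + 0.783²/4) = 0.93, a loss of about 7%. Large-sample simulation with a 5-level gaming scale agrees: 0.27 becomes 0.25, and 0.37 becomes 0.34. With 20% of times tied at the upper limit the ratio is again about 0.93. At n = 60 and an assumed gaming slope of 0.35, power was 64% raw and 69% adjusted.

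**2. Averaging over arms.** Assume 0.37 in the VR arm and 0 under e-learning. The pooled value is about 0.93 × (0.37 + 0)/2 = 0.17, as in simulation. If the e-learning value is 0.185 in the opposite direction, it is 0.93 × (0.37 − 0.185)/2 = 0.09.

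Power follows from Fisher's z with variance 1.06/(n − 3):

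- Pooled, n = 60: atanh(0.17) × √(57/1.06) = 1.26, so power is about 24%.
- VR arm alone, n = 30: atanh(0.37) × √(27/1.06) = 1.96, so power is about 50%.

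A separate simulation with 0.4 in the VR arm only gave 25% and 52%.

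**3. Gender, with no gaming effect.** Assumed: gender–gaming correlation 0 to 0.6, and half the gender gap in time 0 to 0.3 SD. Test results are from 3,000 simulated trials of 60.

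| Gender–gaming correlation | Half gender gap in time (SD) | Spurious pooled coefficient | Raw test significant | Adjusted for arm and gender |
|---|---|---|---|---|
| 0 | 0 | 0 | 5.5% | 5.4% |
| 0.4 | 0.2 | 0.07 | 7.8% | 4.8% |
| 0.6 | 0.3 | 0.16 | 22% | 5.2% |

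If either link is absent, the spurious coefficient is zero.

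**4. What per-arm values can bear.** The coefficient detectable with 80% power is tanh(2.80 × √(1.06/(n − 3))). This is 0.36 at n = 60 and 0.50 at n = 30. A 95% interval around a per-arm coefficient of zero reaches ±tanh(1.96 × √(1.06/27)) = ±0.37. Testing 0.37 against 0 between arms gives 0.388/√(2 × 1.06/27) = 1.39, or about 28% power. Per-arm values can describe, but cannot settle whether the arms differ.

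**The case against.** The strongest reply is that objective 9 asks for a correlation and the plan delivers one. Spearman suits a 5-point scale, and no adjusted or causal gaming effect is promised. Pooling is inferred from silence, and a statistical analysis plan could specify stratified or partial coefficients. Gaming is recorded before randomization, so arm is not expected to confound it. The dilution is only about 7%. The averaging and gender scenarios rest on assumed values.

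Most of this stands, and it makes the point a minor one. It does not remove it, because section 3.5 names a method and, where it wants group or gender accounted for, says so.

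Several stronger readings are tempting, and the protocol does not support them:

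- **A single coefficient answers the objective.** Section 3.5 uses the plural for both coefficients and scales. Two follow if classic means non-VR, four if all items in Table 3 are used.
- **The result is confounded with gender.** It may be. The protocol gives no size for either link, and both are needed.
- **Censoring invalidates Spearman.** Sections 3.2.4 and 3.5 put all censored observations at the same 15 minutes. In a rank correlation they mostly become ties at the slowest rank, which does little harm.
- **The correlation must give way to a Cox model with a group-by-gaming term.** That model would handle censoring formally. With about 60 participants and a model that already holds group, gender, their interaction and two scores, a further interaction would be weakly estimated.

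**Conclusion.** The point holds as a low-severity refinement. The only analysis stated for objective 9 is a set of raw Spearman coefficients without arm or gender. If run on all participants:

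- they lose about 7% of their size at the protocol's own planning effect, assuming equal arms and an outcome that is normal on some scale;
- they average any effect that differs by arm (0.37 and 0 give 0.17);
- they can show a spurious association of 0.07 to 0.16 in the two scenarios where gender is linked to both gaming and time.

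Only the first figure rests on a protocol input. The other two are conditional on assumed values. A reader might infer that objective 9 becomes uninterpretable. That goes too far: the loss of power from dilution is small, the gender bias vanishes if either link is missing, and the result is declared hypothesis-generating.

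**What to change.** In section 3.5, keep the Spearman coefficients and add two things for each gaming scale:

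1. A partial Spearman coefficient adjusted for group and gender: rank both variables, remove group and gender from the ranks, and correlate what remains. This deals with the dilution and the gender bias.
2. The coefficient by arm, reported descriptively with a 95% confidence interval. The partial coefficient still averages over arms, so only this shows whether gaming matters differently for VR and e-learning.

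State that the unadjusted coefficients use all participants. Adding gaming to the Cox model, with a group-by-gaming term, is optional.

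The cost is a sentence or two and a few extra calculations. Every variable is already in Table 3. The downside is more exploratory estimates and wide per-arm intervals, since 30 per arm gives 80% power only for a coefficient of about 0.50. They should be presented as description, without a claim of difference between arms.
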